**2. Data Analysis**

Initial descriptive analyses will be performed considering all variables measured in the study, both quantitative (mean and standard deviation) and qualitative (frequencies and percentages). Subsequently, normality tests will be conducted to determine the appropriate statistical tests for each data set. Appropriate statistical tests will then be applied for each specific analysis.

Subgroup analyses will also be performed, considering variables such as the presence of osteoporosis, osteopenia, high- and low-intensity traumas, smoking, and other comorbidities.

A significance level of 5% probability or the corresponding p-value will be adopted for all tests. All analyses will be conducted using the **SAS for Windows** statistical software, version 9.1.

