**São Paulo, SP**

**2023**

**ABSTRACT**

Among the various complications of the postoperative evolution of fractures of the proximal humerus (FUP) are pain and joint stiffness, generating significant functional limitation in the affected limb. Physical therapy is the standard treatment for both surgical and non-surgical cases. Studies have shown positive effects of photobiomodulation (PBM) on repair and regeneration of fractures, as well as on analgesia and functional improvement. However, they suggest standardization and additional evidence. This randomized controlled double-blind clinical study will aim to evaluate the effects of PBM on the functional recovery of participants with FUP surgically treated with special locking plates. The 42 participants will be randomized (1:1) into 2 groups, the Control group (standardized physiotherapy treatment associated with simulated PBM) and the PBM group (standardized physiotherapy treatment associated with active PBM). The PBM will be applied by the participant at home every day, for 10 minutes, using a device containing 318 LEDs light emitting diodes, 159 LEDs of 660 nm (28.5 mW; 12 J/cm2; 17 J per LED) and 159 850 nm LEDs (23 mW; 10 J/cm2; 14 J per LED). The PBM and physiotherapy sessions (30 minutes, 2 times a week) will be held for 12 weeks. Participants will not be aware of their allocation and will be assessed at 24h, 1, 2, 4, 8 and 12 weeks after the surgical procedure by 4 examiners who are also blinded to each participant's allocation. The main outcome, evaluated in all experimental periods, will be the recovery of shoulder function using the Quick-DASH functional scale. Secondary outcomes will be assessments of range of motion of the shoulder using a digital goniometer, quality of life using the SF-6 questionnaire and the occurrence of adverse effects in all experimental periods. Spontaneous pain, pressure pain (dolorimeter), nocturnal pain and the use of analgesics will be evaluated at 1, 2, 4, 8 and 12 weeks; consolidation of fractures at 4, 8 and 12 weeks through radiographic examinations; and muscle strength by progressive weight bearing at 8 and 12 weeks. In addition to punctual evaluations, each participant will be monitored daily through telephone contact. The collected data will be stored, organized in a repository and the appropriate statistical tests will be applied for each specific analysis. In all tests, a significance level of 5% will be adopted.

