**4.14 Intervention Failure**

Therapy failure will be characterized if any of the following occurs:

1. Inability to apply PBM daily.
2. The participant develops bleeding, sepsis, urticaria, or any discomfort justifying the discontinuation of PBM or placebo PBM.
3. Discontinuation of treatment for any other reason. In these cases, data collected up to that point will be included in the statistical analysis using a mixed-effects regression model.
4. Failure to attend in-person evaluations or respond to scheduled virtual contacts. Data collected up to this point will also be included in the statistical analysis using a mixed-effects regression model.

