**QuickDASH Score Calculation**:

QuickDASH Score=[(Sum of responsesn)−1]×25\text{QuickDASH Score} = \left[\left(\frac{\text{Sum of responses}}{n}\right) - 1\right] \times 25QuickDASH Score=[(nSum of responses​)−1]×25

Where nnn is the number of answered questions.

The QuickDASH will be administered at 1, 2, 4, 8, and 12 weeks post-surgery.

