**4.15.2 Range of Motion**

Shoulder range of motion (ROM) will be assessed on both sides with the participant in an upright position. The maximum tolerated positions in extension, flexion, abduction, adduction, lateral rotation, and medial rotation will be recorded by the evaluator (Figure 9). Rotations will be assessed at 0° abduction and flexion (Gracitelli, 2015; Tenor Junior et al., 2016). All measurements will be performed using a digital goniometer (Kaptron 360, Shenzhen, Dongguan, China).

[figure not shown]

[figure not shown]

[figure not shown]

[figure not shown]

[figure not shown]

[figure not shown]

[figure not shown]

[figure not shown]

[figure not shown]

[figure not shown]

E

A

B

C

D

[figure not shown]

[figure not shown]

F

**Figure.** Measurement of range of motion (ROM) using a digital goniometer during flexion (A), extension (B), abduction (C), adduction (D), lateral rotation (E), and medial rotation (F), with the goniometer in position.

The ROM assessment will be performed 1 day after surgery and subsequently at 1 and 2 weeks through passive movements. During evaluations at 4, 8, and 12 weeks, active movements will be assessed. Results will be recorded on the corresponding clinical forms for each experimental period (**Appendices 3 to 8**).

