**4.15.4 Pain Assessment**

The intensity of spontaneous pain and pain during the function of the injured limb will be evaluated using the visual analog scale (VAS) for pain (Jensen et al., 1986). The chosen scale, represented in Figure consists of a 10 cm numbered line featuring facial expression illustrations, a color gradient, and indications of mild, moderate, and severe intensities to facilitate understanding (Thong et al., 2018).

[figure not shown]

**Figure 11.** Visual analog pain scale.

Pressure pain at the fracture site (**Figure**) will be assessed using a digital algometer (MED DOR, Governador Valadares, MG, Brazil).

[figure not shown]

**Figure 12.** Digital algometer in position for measuring pressure pain.

Results regarding spontaneous pain, pain during function (flexion and abduction), and pressure pain measured using the algometer will be collected 1 day after surgery and subsequently at 1, 2, 4, 8, and 12 weeks. These results will be recorded in the respective clinical forms (Appendices 3 to 8) for each experimental period.

Nighttime pain occurrence will be assessed during daily PBM usage monitoring and recorded in the participant's daily control form (Appendix 2).

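### Normality pre-tests are to choose the test for each data set, and this rule is not reconciled with the mixed-effects model promised for incomplete participants

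*Protocol*

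**What the plan says.** Section 2 (Data Analysis) starts with descriptive summaries and continues: "Subsequently, normality tests will be conducted to determine the appropriate statistical tests for each data set". No outcome is exempted, and no model, primary visit or contrast is named for QuickDASH.

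Section 4.14 (Intervention Failure) sets a different route for incomplete participants. For treatment stopped for other reasons (item 3): "In these cases, data collected up to that point will be included in the statistical analysis using a mixed-effects regression model". For missed assessments or contacts (item 4): "Data collected up to this point will also be included in the statistical analysis using a mixed-effects regression model". Section 2 does not refer to this model.

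On timing, the abstract says participants "will be assessed at 24h, 1, 2, 4, 8 and 12 weeks after the surgical procedure" and adds: "The main outcome, evaluated in all experimental periods, will be the recovery of shoulder function using the Quick-DASH functional scale". Section 4.15.1 says: "The QuickDASH will be administered at 1, 2, 4, 8, and 12 weeks post-surgery". The same section places the questionnaire on the forms in Appendices 3 to 8, which are six forms.

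Pain has a day-1 value; section 4.15.4 says the results "will be collected 1 day after surgery and subsequently at 1, 2, 4, 8, and 12 weeks". So does range of motion (section 4.15.2): "The ROM assessment will be performed 1 day after surgery and subsequently at 1 and 2 weeks through passive movements". Active movement is measured from week 4.

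**The concern.** The pre-test sentence is a positive commitment, not a gap left for an analysis plan. A plan that followed it would let the outcome data decide whether the primary result is a difference in means or a comparison of ranks. A plan that fixed one model would contradict it.

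Section 4.14 adds a second problem. Its promise to use partial data can be kept only if the mixed model is the analysis for everyone, yet section 2 points to tests chosen after looking at distributions. With 42 participants and 15% loss expected, about six people (42 × 0.15 = 6.3) depend on which rule governs. At stake are a single interpretable effect estimate, freedom from choices made after the data are seen, and the use of the partial data.

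**Working it through.** **Side by side.** Section 4.14 assigns a mixed model to items 3 and 4 only. About six people, selected by having stopped or missed visits, cannot give the randomised comparison of arms. The model has to include the complete participants as well. Conversely, a t-test or Mann-Whitney test at a visit uses only people seen at that visit, so it cannot use the earlier data of someone now absent. Each rule, applied literally, prevents the other from doing what it says.

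**The plan's own figure.** Section 4.5 gives 42 participants (21 per group), 5% significance, 90% power and 15% loss, but no effect or SD, so 42 cannot be rebuilt forwards. Working back with 18 evaluable per arm:
- 18 × 1.15 = 20.7, rounded up to 21 per arm, or 42 in total. Dividing instead, 18 / 0.85 = 21.2.
- Implied standardised effect, two-sided: (1.960 + 1.282) × √(2/18) = 1.08. One-sided it would be 0.98; the protocol does not state sidedness.

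**How often the test would switch.** Assumptions, none of them in the protocol: tests chosen visit by visit, Shapiro-Wilk at 5% in each arm, t-test if both arms pass and Mann-Whitney otherwise, 18 per arm.
- Truly normal data, one visit: both arms passed in 90.3% of 5,000 simulated trials, so the test switched in 9.7%.
- Five visits if independent: 1 − 0.903⁵ = 1 − 0.600 = 40% of trials use both kinds of test.
- Five visits with between-visit correlation 0.3, 0.5 and 0.7 (3,000 simulated trials each): 41%, 40% and 38%.

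**What this does to one comparison.** Same rule, 5,000 simulated trials per setting:

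| Data | Type I error | Power at 1.08 | Power of fixed test |
|---|---|---|---|
| Normal | 5.1% | 88.2% | 88.3% (t-test) |
| Skewed (gamma, shape 2) | 5.2% | 92.6% | 92.7% (Mann-Whitney) |

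For one comparison the error rates are essentially unharmed.

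**What a 24 h covariate could add.** Adjusting for a baseline with correlation ρ to the outcome multiplies the residual variance by 1 − ρ². Power ≈ Φ(1.08 × √(18/2) / √(1 − ρ²) − 1.96). The protocol gives no ρ; 0.3 and 0.5 are assumed.
- No adjustment: Φ(3.24 − 1.96) = 90%.
- ρ = 0.3: Φ(3.24 / 0.954 − 1.96) = 92.5%.
- ρ = 0.5: Φ(3.24 / 0.866 − 1.96) = 96.3%.

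**Does the 24 h QuickDASH exist?** The abstract implies that it does. So do the six forms: strength, measured at weeks 8 and 12, is recorded in Appendices 7 and 8, and counting back makes Appendix 3 the day-1 form. The schedule in section 4.15.1 starts at week 1. The document contradicts itself here.

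**The case against.** The strongest defence is that test selection and covariates normally belong in an analysis plan, which is not shown, and that pre-testing does almost no damage to a single comparison. The second part stands, as the table shows: the 40% counts switching, not false positives or lost power. The first part stands for covariates and covariance structure. It does not stand for the pre-test sentence, which the protocol itself fixes.

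Several stronger readings are tempting, but the documents do not support them.
- *The two sections flatly contradict each other.* Section 4.14 names the model only for items 3 and 4 and does not call it primary. They are unreconciled rather than word-for-word opposed.
- *The plan wastes the 24 h baseline.* Section 2 is silent on covariates and excludes none, and whether a 24 h QuickDASH exists is itself unclear. The parent DASH asks about the past week, so a 24 h score would mostly describe the time before surgery and might predict week 12 poorly.
- *Tests will be visit-wise and chosen unblinded.* Visit-wise testing is a natural reading of section 2, but it is not stated. Nor does the section say that the summaries are by arm or unblinded.
- *Range of motion will be tested across passive and active values together.* Section 4.15.2 describes measurement only; no such single test is planned. A comparison of arms at one visit is unaffected.
- *Day-1 values precede treatment.* Sections 4.7 and 4.12 open the envelope and start the device at 24 h, and no order relative to the assessments is fixed.

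**Conclusion.** The point holds in limited form. The protocol commits to data-driven test choice without exempting the primary outcome, and leaves this unreconciled with the mixed model of section 4.14. The harm is an effect measure that can change from visit to visit, room for analyst choice, and no working route for partial data from about six of 42 participants. It is not inflated type I error or lost power in a single comparison.

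The size, 38–41% of trials mixing test types with truly normal data, rests on visit-wise selection, Shapiro-Wilk in each arm and 18 evaluable per arm. The possible gain from a 24 h covariate, from 90% to about 92–96% power, rests on the implied effect of 1.08, assumed correlations of 0.3 to 0.5, and the score being collected before the device is started. This should be changed, and it is mainly a matter of wording.

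**What to change.** - Replace the pre-test sentence in section 2 with one primary analysis: a mixed model for repeated measures on QuickDASH with arm, visit and arm-by-visit, for all participants in the analysis set, complete or not. State one primary contrast, for example week 12 (the end of treatment), with its 95% CI.
- Use an unstructured covariance, with a simpler structure named as fallback if it does not converge.
- Keep residual checks and a rank-based or bootstrap sensitivity analysis as diagnostics. They should not switch the primary analysis.
- Refer to this model in section 4.14, so that both sections describe the same analysis.
- Reconcile the abstract and the form references with the schedule in section 4.15.1 on whether QuickDASH is taken at 24 h. If it is, and it is completed before the device is started, add it as a covariate.
- Use the same approach for pain with its day-1 value, under the same condition on timing.
- If range of motion is modelled over time, analyse passive values (weeks 1 and 2, adjusted for day 1) and active values (weeks 4, 8 and 12) separately.

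The cost is revised wording, slightly more analysis work, and a fixed order for the 24 h assessments relative to the start of the device.
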